### Sample Size Calculation

The sample size calculation for this trial study will be based on the following formula for comparing 2 groups [19]:

where p_1_ = 0.44, p_2_ = 0.33, Z_α/2_ = Z_0.05/2_ = 1.96 (from z table or type 1 error of 5%), Z_β/2_ = z_0.20_ = 0.842 (from z table at 80%), and p = pooled prevalence = (prevalence in intervention group (p_1_) + prevalence in control group (p_2_)/2).

*n* = 300

With a 15% nonresponse rate, the sample size is rounded up to 350 children younger than 5 years being assigned to the intervention group and 350 being assigned to the control group.

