### Data Collection Procedure

Trained interviewers were blinded to group allocation and collected data using pretested questionnaires. For baseline data, a pretested questionnaire was administered to home caregivers on the perception (knowledge, attitudes, and practices) of malaria. This questionnaire will be repeated at the end of the intervention. During the intervention, a structured data collection form will be used and will contain monthly malaria follow-up indicators recorded by home caregivers in the intervention group and the malaria follow-up indicators recorded by CHWs in the control group. The data source for the study will be the malaria register used for the intervention in the Fombap health area and the malaria register used by the CHWs in the Baneghang health area.

In the experimental group (Fombap health area), 6 CHWs were chosen from the Fombap population of 5875 inhabitants, corresponding to 1 CHW per 1000 inhabitants. In each CHW’s zone, the CHW conducted a census of all the households where there is at least one child younger than 5 years and their home caregiver. From this census, children younger than 5 years old and their home caregivers were randomly selected for enrollment in the study. They will be trained in the prevention, diagnosis, and treatment of uncomplicated malaria at home. Malaria kits will be distributed to home caregivers to take care of the children younger than 5 years at home.

With Baneghang health area as the control group, 6 CHWs were also randomly selected from the 9 in the Baneghang health area. In each CHW’s zone, the CHW conducted a census in all the households where there is at least at least one child younger than 5 years and their home caregiver. After the households were identified, children younger than 5 years old and their home caregivers were randomly selected for enrollment in the study. Figure 2 shows the outline of the sampling method for the intervention.

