## Results

In August 2019, 6 CHWs were selected with the help of the community. From September 2019 to October 2019, 408 home caregivers with their 715 children younger than 5 years were identified in the intervention area by CHWs. Among them, 350 children younger than 5 years old and their 203 home caregivers were randomly selected and enrolled in the intervention group. In addition, CHWs identified 451 home caregivers with their 708 children younger than 5 years old. Among them, 350 children younger than 5 years old and their 225 home caregivers were randomly enrolled in the control group.

In the intervention group, 203 home caregivers were trained in November 2019 to prevent and treat malaria at home for their children younger than 5 years. Diagnostic kits (RDTs and thermometers) and treatment (artesunate-amodiaquine and paracetamol) were distributed to these home caregivers during the training. Home treatment effectively started in December 2019 and will continue until May 2020. The baseline data have already been collected and are being analyzed.

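### The sample size treats children as independent although they are nested in caregivers and in 6 CHW zones per arm, so the implied 80% power does not hold once clustering is allowed for

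*Protocol article*

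**What the plan says.** Under Sample Size Calculation the article states: "The sample size calculation for this trial study will be based on the following formula for comparing 2 groups". The inputs are "where p_1_ = 0.44, p_2_ = 0.33", a z-value of "1.96 (from z table or type 1 error of 5"%, a second z-value of "0.842 (from z table at 80"%, and a pooled prevalence. These lead to 300 per arm. The one adjustment is for nonresponse: "With a 15% nonresponse rate, the sample size is rounded up to 350 children younger than 5 years being assigned to the intervention group", with the same number for control. No ICC, cluster size or design effect is listed.

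The Results section reports who was enrolled: "350 children younger than 5 years old and their 203 home caregivers were randomly selected and enrolled in the intervention group", and "350 children younger than 5 years old and their 225 home caregivers were randomly enrolled in the control group". Under Data Collection Procedure, the intervention area was divided among CHWs ("6 CHWs were chosen from the Fombap population of 5875 inhabitants"), and 6 of the 9 CHWs in the control area were drawn at random. In each CHW zone a household census preceded the random selection of children and caregivers. Each arm is a single health area (Study Area).

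Data Management and Analysis plans a t test for means and a chi-square test for proportions, with no term for caregiver or zone.

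**The concern.** A two-proportion formula for independent observations is right only if each child contributes separate information. Here that is doubtful at two levels.

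- **Caregiver.** Siblings share one caregiver. In the intervention arm the caregiver is the person trained, supplied with the kit and reporting results (Steps 3, 4 and 6).
- **Zone.** Children in a zone share one CHW. In the intervention arm the CHW educates, replaces kits and collects indicators (Steps 4 to 6). In the control arm the CHW tests, treats and records (The Control Group; Data Collection Procedure).

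If outcomes are positively correlated within these groups, the effective sample is smaller than the number of children. An analysis that allows for this has less power than the plan implies. An analysis that ignores it has standard errors that are too small and rejects a true null hypothesis too often.

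**Working it through.** **1. Reproduce the plan's figure.** Inputs from Sample Size Calculation: p1 = 0.44, p2 = 0.33, d = 0.11, p̄ = 0.385, z = 1.96 and 0.842. Then 2p̄(1 − p̄) = 0.47355 and p1q1 + p2q2 = 0.2464 + 0.2211 = 0.4675.

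- Pooled: 0.47355 × (2.802)² / 0.0121 = 307.3
- Unpooled: 0.4675 × (2.802)² / 0.0121 = 303.3
- Pooled null, unpooled alternative: (1.96√0.47355 + 0.842√0.4675)² / 0.0121 = 306.1

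The stated 300 is within about 2% of these. The formula itself is missing from the text available, but independent children already need slightly more than 300, so no design effect can be hidden in it. For nonresponse, 300 × 1.15 = 345 and 300 / 0.85 = 353, so 350 is fair.

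**2. Reserve left.** 350 × 0.85 = 297.5. With power = Φ[(d − 1.96√(0.47355/n)) / √(0.4675/n)]:

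- n = 297.5: (0.11 − 0.0782) / 0.0396 = 0.80, power 79%
- n = 300: 79%
- n = 350 (no loss): 85%

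At the planned loss, any positive ICC lowers power further below 80%.

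**3. Were siblings enrolled together?** Enrolled children per caregiver are 350/203 = 1.72 and 350/225 = 1.56. The census gives 715/408 = 1.75 and 708/451 = 1.57. The close match suggests so. Drawing children singly would be expected to reach about 264 and 279 caregivers (simulation, with second and later children spread at random over caregivers).

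**4. Caregiver clustering alone.** Design effect (DE) = 1 + (m − 1) × ICC, with m = 1.72 and 1.56. The ICCs are assumptions.

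| ICC | DE (int. / control) | Power, 297.5 per arm | Power, 350 per arm |
|---|---|---|---|
| 0.2 | 1.14 / 1.11 | 74% | 81% |
| 0.5 | 1.36 / 1.28 | 67% | 74% |

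**5. Zone clustering alone.** Assumptions: the ICC, 12 exchangeable zones, equal zone size (297.5/6 = 49.6, or 350/6 = 58.3), and a cluster-adjusted test. The 10 degrees of freedom (df) are 12 zones minus 2. The detectable difference is measured from 33% at 80% power (normal approximation).

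| ICC | DE at 297.5 | Effective n | Power (10 df) | Detectable difference | Power at 350 (10 df) |
|---|---|---|---|---|---|
| 0.01 | 1.49 | 200 | 62% (54%) | about 14 points | 67% (58%) |
| 0.02 | 1.97 | 151 | 50% (43%) | about 16 points | 53% (46%) |
| 0.05 | 3.43 | 87 | 32% (27%) | about 21 points | 33% (28%) |

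**6. Both levels.** Caregiver ICC 0.3 and zone ICC 0.01, with 700/428 = 1.64 children per caregiver: DE = 1 + 0.64 × 0.3 + (49.6 − 1.64) × 0.01 = 1.67, power 57%.

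**7. The planned chi-square test.** If it ignores zones, its type I error is 2[1 − Φ(1.96/√DE)]. With DE 1.49, 1.97 and 3.43, 1.96/√DE is 1.61, 1.40 and 1.06, giving about 11%, 16% and 29%.

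**8. When 80% survives.** With all 350 per arm analysed, the tolerable DE is 350/306 = 1.144. That allows a caregiver ICC (alone) up to 0.144/0.64, about 0.23, or a zone ICC (alone) up to 0.144/57.3, about 0.0025.

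**The case against.** **The arithmetic.** A reader might infer that 300 or 350 is miscalculated. Neither is: both are ordinary rounding of the stated inputs. The omission is the design effect.

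**Zones as sampled clusters.** The zone figures need inference beyond these zones. Six CHWs at about one per 1000 inhabitants appear to cover all of Fombap, and only the control arm sampled zones (6 of 9). If inference is limited to the two areas, intervention zones act as strata and control zones carry a finite-population factor of 1/3. The variance factors become 1 − ICC and (1 − ICC) + 49.6 × ICC/3. With SE² = (0.2464f₁ + 0.2211f₂)/297.5 and power Φ(0.11/SE − 1.96), power is about 77%, 74% and 67% at ICC 0.01, 0.02 and 0.05. This stands: the loss is then much smaller, though power is still below 80%. The article does not say which inference is meant or how many children came from each zone.

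**Full 15% loss.** All 350 per arm were enrolled, and loss may be lower than planned. This stands, so both bases are shown.

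**Whole households.** The article says only that children and their caregivers were randomly selected. Joint enrolment of siblings is inferred from the counts. The zone result does not depend on it.

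**A misread null result.** A reader might infer that a non-significant result would be taken as equivalence. The article does not support this. It states a superiority hypothesis and nowhere treats non-significance as equality. Under the test actually planned, the more direct risk is a false positive.

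**Precision.** The proportions 0.44 and 0.33 are not tied to a named indicator, and some listed indicators need not have all enrolled children as denominator. The percentages therefore illustrate the size of the loss; they do not predict it.

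**Conclusion.** The point holds in a limited form. The calculation assumes independent children, applies no design effect and leaves no reserve after the planned nonresponse, so 80% power for 0.44 v 0.33 is not supported for a valid, cluster-adjusted analysis.

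Given positive ICCs, the direction of the loss is secure. Its size is not, because the article gives no ICC. Caregiver clustering alone costs little to moderate power, and 80% can survive it if there is no loss and the ICC is about 0.2 or less. Zone clustering could cost much more, under the conditions named in step 5. Variation between the two health areas comes on top and cannot be estimated with one area per arm. Keeping the plain chi-square test does not rescue the power claim, because it exchanges lost power for an inflated type I error.

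**What to change.** Keep 350 children per arm. In Sample Size Calculation:

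- Replace the unqualified 80% basis with the effective sample size, power and detectable difference over a stated range of caregiver and zone ICCs (for example zone 0.01 to 0.05).
- Name the assumptions: zone sizes, expected loss, degrees of freedom, and whether inference extends beyond the enrolled zones.
- State that variation between the two areas is not included.

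In Data Management and Analysis, replace the plain chi-square comparison with one that accounts for clustering by caregiver and zone, suited to as few as 6 zones per arm, and tie the restated power to it.

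The cost is a rewritten paragraph and a changed test. The stated power becomes less favourable and intervals become wider. No extra enrolment is needed.

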### Inclusion and Exclusion Criteria

The inclusion criteria will be households with at least one child younger than 5 years and their home caregivers who are between 18 years and 60 years of age and who take care of these children.

The exclusion criteria will be children younger than 2 months and home caregivers who do not give their consent.

### Data Collection Procedure

Trained interviewers were blinded to group allocation and collected data using pretested questionnaires. For baseline data, a pretested questionnaire was administered to home caregivers on the perception (knowledge, attitudes, and practices) of malaria. This questionnaire will be repeated at the end of the intervention. During the intervention, a structured data collection form will be used and will contain monthly malaria follow-up indicators recorded by home caregivers in the intervention group and the malaria follow-up indicators recorded by CHWs in the control group. The data source for the study will be the malaria register used for the intervention in the Fombap health area and the malaria register used by the CHWs in the Baneghang health area.

In the experimental group (Fombap health area), 6 CHWs were chosen from the Fombap population of 5875 inhabitants, corresponding to 1 CHW per 1000 inhabitants. In each CHW’s zone, the CHW conducted a census of all the households where there is at least one child younger than 5 years and their home caregiver. From this census, children younger than 5 years old and their home caregivers were randomly selected for enrollment in the study. They will be trained in the prevention, diagnosis, and treatment of uncomplicated malaria at home. Malaria kits will be distributed to home caregivers to take care of the children younger than 5 years at home.

With Baneghang health area as the control group, 6 CHWs were also randomly selected from the 9 in the Baneghang health area. In each CHW’s zone, the CHW conducted a census in all the households where there is at least at least one child younger than 5 years and their home caregiver. After the households were identified, children younger than 5 years old and their home caregivers were randomly selected for enrollment in the study. Figure 2 shows the outline of the sampling method for the intervention.

**Figure 2 figure2:**
[figure not shown]
Flow chart showing the sampling method for the intervention study.

### Ethical Considerations

Ethical approval has been obtained from the Faculty of Health Sciences Institutional Review Board of the Buea University (reference no. 2019/1023-09/UB/SG/IRB/FHS). Administrative authorization has been obtained from the University of Buea, the Regional Delegation of Public Health for the West Region, and the health districts of Santchou and Penka-Michel.

Participation of individuals and households will be strictly voluntary and on the basis of informed written consent and assent by the household heads or caregivers. The purpose of the study and the role of the participants will be well explained in the consent form. Once informed consent and assent are obtained from the participants, research staff will collect baseline data, and will conduct the intervention and postintervention.

### Intervention Development

In order to contribute to the improvement of the HMM component of the integrated CDI strategy, an intervention will be implemented to make home caregivers accountable for the malaria prevention, diagnosis, and treatment at home. This strategy will be used in the Fombap health area where the integrated CDI strategy will not be implemented. The intervention was designed with the active participation of CHWs and home caregivers in the management of malaria at home through their training. Participants in this study will be made aware that the training they receive will give them the opportunity to test and treat malaria in their children younger than 5 years of age at home. Thus, this intervention will enhance home caregivers’ capacities to prevent, diagnose, and treat malaria at home in their children younger than 5 years. The different steps will be the selection of CHWs, the census of households with at least one child younger than 5 years and their home caregivers, the training of CHWs and home caregivers, the provision and the management of malaria kits, the health education of home caregivers on malaria prevention measures, and the monitoring and evaluation of the activities.

#### Step 1: The Selection of Community Health Workers

In the intervention group, the identification and selection of CHWs will be carried out in collaboration with the head of the health area and the leaders of all communities. A meeting will be convened at the Fombap Higher Chiefdom during which CHWs in each community will be selected. Then, 6 CHWs will be selected in the intervention group and 6 CHWs will be randomly selected among the 9 existing in the control group.

#### Step 2: The Census of Households, Children Younger Than 5 Years, and Home Caregivers

The CHWs in their respective zones identified and recorded all households with at least one child younger than 5 years and their home caregivers. After identifying the households, the children younger than 5 years and their home caregivers were randomly selected by the researchers for enrollment in the study.

#### Step 3: The Training of CHWs and Home Caregivers

The selected CHWs will be trained by the research team, and home caregivers will be trained by the research team with the help of the CHWs. The training will be focused on malaria management of children younger than 5 years at home and will include recognizing uncomplicated malaria (base on sign and symptoms), performing malaria RDT, administering artesunate-amodiaquine to children in the case of a positive test, and referring RDT-negative children or those with severe malaria to the health care center. The training process will be based on the training handbook of the Cameroon Ministry of Public Health. The training module of the CHW modified version will be used, as it is simple and has practical demonstrations to enhance understanding. The algorithm used in our study (Figure 3) will be adapted from that used in Senegal [10].

**Figure 3 figure3:**
[figure not shown]
Algorithm for the home management of malaria adapted from that used in Senegal. ACT: artemisinin-based combination therapy; RDT: rapid diagnosis test.

#### Step 4: The Provision and Management of Malaria Kits

SD Bioline Malaria Ag Pf RDT is used in Cameroon and meets the performance criteria recommended by the WHO [20], while a fixed dose of artesunate-amodiaquine is a combination used as first-line treatment in Cameroon [21]. RDTs and malaria kits will be distributed during the training to all home caregivers, and then the CHWs will take care of replacing kits in households. The malaria kits will be provided to CHWs by the research supervisor according to the need expressed. The support kit will consist of a thermometer, 2 RDTs, a packet of 25 mg/67.5 mg of artesunate-amodiaquine and/or 50 mg/135 mg of artesunate-amodiaquine, a packet of paracetamol, and an algorithm chart for malaria management. In case of any fever above 38ºC in the children younger than 5 years of age as confirmed by the thermometer and without any other sign of gravity, the home caregiver will conduct an RDT of malaria. If the test result is positive, the caregiver will administer the child artesunate-amodiaquine and paracetamol; if the result of the test is negative, the caregiver will take the child to a health center for in-depth exams and treatment for the other causes of fever. For statistical purposes and to replace their kits, home caregivers will inform the CHW of their community by phone of the results of the test and the treatment received by their child. Malaria kits will be distributed free of charge for children younger than 5 years old and this will be purchased from the national provision fund. This study is funded by [name].

#### Step 5: The Health Education of Home Caregivers

CHWs will provide health education to the home caregivers concerning malaria prevention measures, the advantages of HMM, and the role of home caregivers in the health care of children. Health education will focus on malaria prevention measures, such as cleaning around the house, the use of insecticide-treated mosquito nets, the use of window screens, the use of insecticides, and the closure of doors and windows before nightfall. CHWs will also explain the concept of home-based prevention and treatment of malaria and the possibility of treating uncomplicated malaria in the community and even in the home. They will also explain that if the diagnosis and treatment of uncomplicated malaria occurs within 24 hours, the condition usually progresses to cure, whereas if early diagnosis and treatment do not occur, the condition can progress to severe malaria and even death. CHWs will provide health education to home caregivers by going door-to-door once a week to at least 5 households and will also go once a month to meetings of women in their area. They will also go to replace the malaria kits in any household that has a suspected case.

#### Step 6: Monitoring and Evaluation Activities

The monitoring of the activities will be carried out by the research supervisor, the head of the health area, and the researchers to compile and evaluate the work completed on the field. A meeting will be organized twice a month, bringing together the research supervisor and the CHWs to monitor activities. For statistical purposes and to replace their kits, home caregivers will inform CHWs in their community of all suspected malaria cases in the children younger than 5 years, of the result of RDTs, and of the malaria treatment received by the child. Each month, the monitoring indicators produced by the home caregivers will be collected by CHWs for evaluation purposes. An evaluation of the activities will be carried out monthly during the period of intervention.

After the intervention, a descriptive, analytical, and comparative study will be made in the Baneghang and Fombap health areas to compare the two strategies. This evaluation will be based on the HMM follow-up indicators reported by home caregivers in the intervention group and will be compared to those of the CHWs in the control group.

### The Control Group

The integrated CDI strategy is implemented in 5 health districts in the West Cameroon region, including the Penka-Michel Health District, from which our control health area, Baneghang, was randomly selected for the site of the control group. In this area, the malaria management component of the integrated CDI strategy is carried out by 9 CHWs, 6 of whom were randomly selected for the study. CHWs conducted a census in their respective zone of all the households where there is at least one child younger than 5 years and their home caregivers. After identifying the households, children younger than 5 years old and their home caregivers were randomly selected for enrollment in the study.

Usually, when there is a suspected case of malaria in the community, the patient is taken to the CHW's home. The patient is examined by the CHW to check for uncomplicated malaria. If the test is positive, the CHW conducts an RDT and administers malaria treatment; if the test is negative, the CHW refers these patients and those with severe malaria to the health care center and makes home visits to provide health education to parents.

